### Intervention

#### HCA training in relational care: Older People’s Shoes

HCAs from wards randomised to the new training intervention (*n* = 6 wards, 2 wards per hospital) will receive ‘Older People’s Shoes’, a newly developed HCA training package that focuses on the relational care of older people. The training intervention was developed using evidence from interviews with HCAs, other ward staff, older people, and a panel of experts. The intervention development work was funded by the same grant but in an earlier phase of this project. Course materials comprise a trainer manual and trainee workbook, PowerPoint resources and an online version of the training.

Training will take place during weeks 5 to 8 post-randomisation after the 4-week set-up period. It comprises 2 training days approximately 1 week apart. Older People’s Shoes training is delivered by registered nurses, all of whom are employed at the local Hospital Trust in practice development or education and training roles. These trainers receive full training in the content and delivery of ‘Older People’s Shoes’ from members of the research team.

Training comprises three units relating to the care of older people in hospital:Walking in Older People’s Shoes.This unit helps HCA learners to understand the challenges of being an older person in hospital. Patients’ experiences are brought to life using videos and narratives in which real older patients talk about their experiences (both good and bad) of hospital care. Experiential learning is provided through learners having the opportunity to use age simulation suits.Getting to know older people.This unit challenges HCA participants to think about how hospitalisation can strip away much of what makes people individual; and how stereotypical notions of ageing may lead care staff to make false or limiting assumptions about older people. It looks at how opportunities can be found to ‘discover the person behind the patient’ through life stories, and so build stronger relationships with the older people they care for.Learning from customer care.This unit asks HCA participants to consider how some aspects of customer care provided in non-health settings can be applied to their work in the ward. This includes ‘active listening’ and reading body language to try to understand what may lie behind the behaviour of patients that are seen as ‘difficult’; and how to deal with angry patients or visitors. The aim is that learners will come to understand how relatively simple techniques can be incorporated into their own practice. The unit also addresses the need for HCAs to look after themselves.

Each unit is divided into two sessions, one per day, so that learning on the first day can be consolidated and developed during the second day. At the end of Day 1 HCAs are asked to undertake brief individual work-based exercises prior to Day 2. Additional materials are also available online with access restricted to HCAs allocated to the training intervention.

Training seeks to promote empathy with older patients, give time for reflection and shared experience, affirm the importance of the HCA role, and ensure that HCAs know how to access their local support network for any issues that may arise as a result of the training intervention. Given the practical, hands-on nature of much of an HCA’s work, the overarching theoretical basis for the training package is derived from Carver’s framework for understanding experiential education [37]. Carver’s four key elements to experiential education are applied throughout the training intervention:Authenticity – activities are directly relevant to the participant HCA’s role in caring for older people in hospital.Active learning – group exercises are embedded throughout to maintain HCA participant engagement and ensure learning is active rather than passive.Drawing on experience – HCA participants are encouraged to think about what happened to them in particular situations, how it felt, how they reacted, what resulted, and what they observed.Provision of mechanisms for connecting experience to future opportunity – HCA participants are encouraged to reflect on their participation in learning activities to make their experiences relevant to their future work with older people.

The pedagogical approach used to inform the design of the training intervention was Gagne’s nine-step model [25] (gain attention, identify objective, recall prior learning, present stimulus, guide learning, elicit performance, provide feedback, assess performance, enhance retention/transfer). The ' Older People’s Shoes' training intervention used this model in a reduced form to structure individual learning activities: learning objective, trigger, content, guided practice/reflection, key messages.

### Training as usual

HCAs from wards not randomised to the training intervention (*n* = 6 wards, 2 wards per Trust) will receive ‘training as usual’. This is typically restricted to periods of staff induction or focussed on mandatory training requirements such as manual handling. HCAs will receive no training in relational care beyond any that might be experienced as part of the standard process within their employing NHS Hospital Trust. Educational leads for each NHS Hospital Trust have provided details of how this is operationalised for HCAs within their organisation.

### Outcomes

Outcomes at all levels (ward, HCA and patient) will be observed during weeks 9 to 12 after randomisation. The primary outcome is at the level of patient (PEECH score).

#### Wards

Between weeks 9 and 12 post-randomisation, 8 observations per ward will be conducted using identical methods to those used in the baseline period.

#### Healthcare assistants

HCAs will receive the TEQ and AGED inventory twice during the follow-up period, at weeks 9 and 12 post-randomisation.

#### Patients

Patients due to be discharged from enrolled wards between weeks 9 and 12 post-randomisation will be approached, recruited and administered questionnaires in an identical way to that used in the baseline period.

#### Measures of cost and cost-effectiveness

HCA staff in the intervention arm will be asked in the follow-up questionnaire whether the average duration of their patient contact times has changed since they received the training in relational care. Ward records will be used to ascertain the number of days patients stayed in the ward. Associated analysis will focus on completion rates in order to identify the feasibility of collecting such data, and inform the design of any future definitive study. Appropriate unit costs (e.g. Curtis [38]) will also be attached to all items of resource-use in order to enable the overall costs to be estimated and thereby identify important cost drivers. Completion rates for the EQ-5D-5 L will be used to assess whether it is appropriate for this population group, and the extent to which a future definitive cluster randomised controlled trial would be better designed as a cost-consequences analysis, where the incremental cost would be presented in relation to ward, HCA and patient outcomes as appropriate.

#### Qualitative interviews of trainers and HCAs

Following the delivery of the intervention, trainers will be asked to undertake a semi-structured qualitative interview. These interviews will follow a topic guide covering specific aspects of delivering the intervention and more general aspects about learner engagement. Directly after the follow-up period a sub-sample of HCAs who have undertaken the training intervention will be asked to undertake a semi-structured qualitative interview. These interviews will follow a topic guide covering experiences of both the training intervention itself and being part of the pilot trial.

All qualitative interviews are expected to last between 30 and 45 minutes. They will be conducted by a member of research staff, and be audio-recorded if given permission to do so by the interviewee.

### Sample size

As the study is to test feasibility and is a pilot cluster randomised controlled trial, it is not powered to determine superiority of HCA training in relational care or training as usual.

#### Wards

Observations by a researcher employed on the grant will take place on the four enrolled wards at each participating NHS Hospital Trust. For each ward, eight observations will take place during the baseline period and eight during the follow-up period. Each observation will last for 50 minutes.

#### HCAs

All eligible HCAs will be invited to take part. Numbers of HCAs employed on wards varies within and between NHS Hospital Trusts. Assuming approximately 10 HCAs employed on each enrolled ward, and an estimated recruitment rate of 70 %, it is anticipated that 84 HCAs will be recruited (42 per arm). A total of 12 HCAs from the intervention arm will be invited to take part in a semistructured interview. Anticipating that there will be some shortfall between recruitment to training and uptake of training, this number represents approximately one third of expected trainees. Requesting interviews with a greater number would put undue strain on ward staffing levels. Of those HCA trainees who give initial consent to interview, purposive sampling will be used to select across NHS Hospital Trusts, and to maximise variation of interviewees in terms of gender and length of experience.

#### Patients

It is anticipated that across all 3 NHS Hospital Trusts 100 patients will receive questionnaires during the 4-week baseline period and a further 100 patients will receive questionnaires during the 4-week follow-up period.

#### Trainers

All trainers (one or two per NHS Hospital Trust) who deliver the training intervention will be asked to take part in follow-up semi-structured interviews.

### Fidelity

All training intervention sessions will be observed by at least one member of the research team. Deviations from the trainer guide will be recorded. In addition, one member of the research team will observe the training intervention being delivered at each of the three centres to record differences in delivery between trainers. For those HCAs who attend the training intervention days, the number of days actually attended will be recorded.

### Statistical analysis

Within the analysis plan, the emphasis will be on the estimation of parameters required for a future sample size calculation and potential differences via confidence intervals, rather than formal hypothesis testing.

#### Ward-level analysis

QUIS will be analysed as a total mean rating for each observed session. Analysis will be based on the change from baseline to outcome using a general linear model including NHS Hospital Trust as this was a stratification variable. Due to the small number of wards this analysis will be descriptive.

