### Aims of the study

The aims of the study are to assess the feasibility of a cluster randomised controlled trial to compare the performance of an HCA training package in relational care against current training in improving the care of older patients in acute NHS settings, and to explore optimal methods for cost-benefit analysis for a definitive study.

Important parameters that are needed to inform the feasibility of a definitive trial (and if feasible, then the design of such a trial) [28] will be assessed:The acceptability of the intervention to trainers and HCA trainees.The willingness of ward managers, HCAs and older patients to participate in a cluster randomised controlled trial.The willingness of ward managers for wards to be randomly allocated.The level of non-response and item non-response to outcomes at the level of ward, HCA and patient.The acceptability of outcome measures to participants.The ability to monitor levels of resource-use and quality of life data.The variability within and between ward, HCA and patient outcomes.The appropriateness of ward as the unit of randomisation.

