### Recruitment

#### Wards

The ward manager provides permission for ward participation. Recruitment of wards will cease once permission is given by ward managers of 4 eligible wards from each of 3 acute NHS Hospital Trusts (*n* = 12 wards in total).

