### Baseline measures

#### Wards

To assess quality of interactions within a ward the Quality of Interaction Schedule (QUIS) observation tool is used by a trained observer at each hospital [29]. QUIS is an observational strategy in which interactions between patients and care staff are coded as positive social (interactions involving conversation and companionship), positive care (interactions during the appropriate delivery of care), neutral (brief and indifferent interactions), negative protective (keeping safe without explanation or reassurance) or negative restrictive (opposing or resisting patients’ freedom of action without good reason). Ward observations take place over the 4-week period prior to randomisation. Each observation is conducted over a 50-minute period by 1 observer. The interactions observed are those that involve a patient and at least one HCA. Eight observations per ward will be conducted during the baseline period. Observations take place during mornings, mealtimes and visiting periods. On four occasions at each hospital, observations will be conducted in pairs to assess inter-rater reliability.

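### The QUIS analysis names the session as its unit and change from baseline as its outcome, with no ward term; these do not fit together, and the model as stated cannot separate within-ward from between-ward QUIS variance

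*Protocol article*

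**What the plan says.** On the QUIS, the protocol article's Ward-level analysis section states three things.

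- Unit: "QUIS will be analysed as a total mean rating for each observed session".
- Outcome and model: "Analysis will be based on the change from baseline to outcome using a general linear model including NHS Hospital Trust". Trust is there because it was a stratification variable. No ward term, fixed or random, is named.
- Status: "Due to the small number of wards this analysis will be descriptive".

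The design comes from other sections. Recruitment (Wards) gives "4 eligible wards from each of 3 acute NHS Hospital Trusts", so 12 wards. Sample size (Wards) gives "For each ward, eight observations will take place during the baseline period and eight during the follow-up period". Allocation for trial interventions makes the ward the unit of randomisation, stratified by Trust.

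Two sections say what the analysis is for. Aims of the study lists, among the parameters to be assessed, "The variability within and between ward, HCA and patient outcomes". The opening of Statistical analysis says that "the emphasis will be on the estimation of parameters required for a future sample size calculation and potential differences via confidence intervals", in preference to formal testing.

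The HCA-level and patient-level sections give TEQ, AGED and PEECH a linear mixed model with ward as a random effect. They say that this handles dependence within a ward and yields the variance estimates needed to plan a future trial.

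**The concern.** The stated unit and the stated outcome do not match. A baseline session and a follow-up session on the same ward are separate occasions, possibly involving different patients and staff, and the article describes no pairing. A session therefore has no change from baseline. An analyst must either fit session values with terms for period and arm, or average to ward level and take differences. The text does not say which.

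Two things depend on this. On the session reading, with no ward term, sessions from one ward count as independent although the ward was randomised, and the interval for the arm difference can be too narrow. On both readings the model has a single residual variance. A pilot whose emphasis is on parameters for the next sample size calculation would then not obtain, from its stated QUIS model, the split needed to weigh more wards against more sessions per ward.

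**Working it through.** The article gives no variance, ICC or precision figure for the QUIS, so there is no stated result to reproduce.

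**Counts from the design.** 3 Trusts × 4 wards = 12 wards. 12 × 8 = 96 sessions per period, and 96 × 2 = 192 in all.

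**Assumed quantities.** ICC, the share of session-level variance lying between wards within a period: 0.05 to 0.30. r, the correlation of a ward's effect between baseline and follow-up: 0 to 1. The article gives neither.

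**Reading 1: session values, no ward term.** Set the total session variance to 1.

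- True variance of one ward's change in mean: 2(1 − ICC)/8 + 2·ICC·(1 − r).
- Variance if the sessions are taken as independent: 2/8.
- Ratio, true to naive: (1 − ICC) + 8·ICC·(1 − r) = 1 + 7·ICC − 8·ICC·r.

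The ratio equals 1 at r = 7/8. Below that the naive interval is too narrow, and above it slightly too wide. Example at ICC 0.20 and r = 0.5: 1 + 1.40 − 0.80 = 1.60.

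Coverage of the nominal 95% interval was simulated: 4,000 trials per setting with no true effect, and ordinary least squares on 192 sessions with Trust, arm, period and arm × period. Each cell shows variance ratio / coverage.

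| ICC | r = 0 | r = 0.5 | r = 0.8 | r = 1 |
|---|---|---|---|---|
| 0.05 | 1.35 / 91% | 1.15 / 93% | 1.03 / 94% | 0.95 / 95% |
| 0.10 | 1.70 / 86% | 1.30 / 91% | 1.06 / 94% | 0.90 / 96% |
| 0.20 | 2.40 / 78% | 1.60 / 87% | 1.12 / 93% | 0.80 / 97% |
| 0.30 | 3.10 / 71% | 1.90 / 83% | 1.18 / 91% | 0.70 / 97% |

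The r = 0 column is the familiar single-period design effect, 1 + 7·ICC. It is the worst case for a change analysis, not the typical one.

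**Reading 2: 12 ward-level changes.** With three Trust means and one arm effect, the residual degrees of freedom are 12 − 4 = 8 and t = 2.31. In the same simulations, coverage was 94% to 95% at every ICC and r tried.

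**Variance components.** Under reading 1, the residual pools ward and session variation into one number. Under reading 2, the residual variance is 2 × (within/8 + between), where between is the part of the ward variance that is specific to a period. Different pairs give the same value:

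- between 0, within 1.0: 2 × (0.125 + 0) = 0.25
- between 0.05, within 0.6: 2 × (0.075 + 0.05) = 0.25
- between 0.10, within 0.2: 2 × (0.025 + 0.10) = 0.25

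So neither model identifies the two variances separately.

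**The case against.** The strongest reply is that ward-level change was intended. The section is headed as a ward-level analysis, its caveat is the small number of wards rather than of sessions, and change can only be formed directly at ward level. This is plausible, and it stands: on that reading sessions are not treated as independent and the intervals are sound.

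A second reply is that the list of terms is not exhaustive. The intervention is not named either, and a condensed article may leave the full model to an analysis plan. This has some force against reading the missing ward term as a deliberate choice. Yet the article does specify a general linear model here and, in the next two sections, mixed models with a random ward effect and a stated purpose. The contrast is in the text, and so is the mismatch of unit and outcome.

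A third reply is that the analysis is descriptive, the pilot is not powered, and the primary outcome is PEECH, whose variance components are planned. This lowers the stakes. It does not supply the missing quantity: variance components are themselves descriptive estimates, and the aim on variability names ward outcomes as well.

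Lastly, the HCA-level section contains a sentence on sensitivity analysis using per-ward averages and sub-types, which may be displaced QUIS text. It sits under the HCA heading and does not name the QUIS, and ward averages would not give the within-ward variance.

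**Conclusion.** The point holds as a defect of specification that should be corrected. The unit and the outcome do not fit together, and on either reading the stated model does not deliver the within-ward and between-ward QUIS variability that the article sets out to assess. The second conclusion needs no assumed figure.

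The effect on the confidence interval is conditional. It arises only if sessions are analysed without ward, and its size depends on an assumed ICC and r: coverage of about 91% to 71% at r = 0, 93% to 83% at r = 0.5 and 94% to 91% at r = 0.8, and slight conservatism above r = 7/8.

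A reader might infer that the QUIS intervals will certainly be too narrow, with coverage in the seventies or eighties. The documents do not support that, because the ward-level reading is open and such figures need a sizeable ICC together with ward effects that are weakly or only moderately correlated over time. Nor does it follow that the pilot cannot yield the variances. The session values will be collected; only the stated model fails to use them for this. Using change from baseline, or averaging ratings within a session, is not in itself an error.

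**What to change.** State the unit of analysis. Then analyse the 192 session means in a linear mixed model with period, arm × follow-up and Trust as fixed effects, and ward as a random effect, adding ward-by-period if it can be estimated. Use small-sample degrees of freedom. Report the between-ward and within-ward variances with intervals. This brings the QUIS into line with the models for TEQ, AGED and PEECH.

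Alternatively, keep the ward-level change with Trust and arm for the contrast, say explicitly that it is computed from ward means, and report the variance components from the mixed model beside it.

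The cost is a change of wording and a little more analysis, with no new data. Variance estimates from 12 wards will be imprecise, so the intervals should accompany them into any later sample size calculation.

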#### HCA-level analysis

The outcomes of TEQ and AGED will be assessed using a linear mixed-effect model, with fixed effect being the intervention and the random effect will be ward. This will account for the potential of dependence of HCA-level responses from HCAs within the same ward. Additionally, the baseline value of the outcome will also be included as a fixed effect in a sensitivity analysis. These models will allow the estimation of the parameters required, including the within-ward and between-ward variance, for the planning of future trials, including the HCA-level variation and between-ward variation.

Due to the small number of clusters, the results of the random-effect model will also be compared to those using a generalised estimating equation (GEE) model. Additionally, as the number of clusters is less than 15 per arm [39], sensitivity will be analysed as a total average, per ward, rating as well as the individual sub-types. Due to the small number of wards involved this analysis will be descriptive. Additionally, the sensitivity of the assumption of a normally distributed outcome will be assessed using the two-stage, non-parametric bootstrap.

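### QUIS is analysed as change from baseline; adjusting follow-up for the ward's baseline mean would usually be somewhat more precise and costs only a wording change

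*Protocol article*

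**What the plan says.** The Ward-level analysis section first sets the unit of measurement: "QUIS will be analysed as a total mean rating for each observed session". It then fixes the analysis: "Analysis will be based on the change from baseline to outcome using a general linear model including NHS Hospital Trust". It closes with: "Due to the small number of wards this analysis will be descriptive". Baseline QUIS is not named as a covariate, either in the main analysis or in a sensitivity analysis.

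The design inputs come from elsewhere in the protocol article. Recruitment (Wards) stops at "4 eligible wards from each of 3 acute NHS Hospital Trusts", which makes 12. The Intervention and Training as usual sections give two wards per arm in each Trust. Sample size (Wards) sets the observations: "For each ward, eight observations will take place during the baseline period and eight during the follow-up period".

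Three other statements bear on how much this matters. The opening of Statistical analysis puts the emphasis on planning parameters and on differences shown with confidence intervals, not on testing. Outcomes names the patient-level PEECH score as primary. Sample size says that the pilot is not powered for superiority.

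**The concern.** A change score is a baseline adjustment with the coefficient forced to 1. That is right only if a ward's follow-up mean moves one for one with its baseline mean. Each baseline here averages eight 50-minute sessions, so part of the spread between wards at baseline is sampling noise, and subtracting the baseline puts that noise into the outcome.

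Two things follow, and they are two views of the same loss. The interval for the arm difference is usually wider than it need be. And once the baselines are known, an arm that started high by chance will tend to show a smaller change for that reason alone. With six wards per arm, chance imbalance at baseline is likely. At stake are the QUIS estimate and its interval, in a pilot whose stated purpose is estimation.

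**Working it through.** **No figure to reproduce.** The protocol gives no standard deviation, correlation, intraclass correlation (ICC) or target difference for QUIS. The comparison below is therefore relative, across a range of assumed r.

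**Inputs from the protocol.** 12 wards, 3 Trusts, 2 v 2 wards per Trust, 8 sessions per ward per period. Baseline and follow-up sessions are not stated to be paired, so change is taken at ward-mean level.

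**Assumptions.** Ward means have equal variance (σ²) in the two periods, with correlation r within Trust and arm.

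**Step 1: what r might be.** If sessions are exchangeable within a ward and period, with session ICC ρ, and true ward levels in the two periods correlate at π, then r = π × 8ρ/(1 + 7ρ).

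| ρ (assumed) | r at π = 1 | r at π = 0.8 |
|---|---|---|
| 0.05 | 0.40/1.35 = 0.30 | 0.24 |
| 0.10 | 0.80/1.70 = 0.47 | 0.38 |
| 0.20 | 1.60/2.40 = 0.67 | 0.53 |
| 0.30 | 2.40/3.10 = 0.77 | 0.62 |

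Even at ρ = 0.5 and π = 1, r is 4.0/4.5 = 0.89.

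**Step 2: variance of the arm difference** (6 v 6 wards, so 1/6 + 1/6 = 1/3).
- Follow-up only: σ²/3.
- Change: 2(1 − r)σ²/3. This exceeds follow-up only whenever r < 0.5.
- Baseline-adjusted: (1 − r²)(1 + 1/6)σ²/3. The 1/6 is the price of estimating the slope with this few wards.

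**Step 3: interval ratio, adjusted to change.** Residual degrees of freedom are 12 − 3 − 1 = 8 for change (t = 2.306) and 7 with baseline added (t = 2.365). The ratio is √[((1 + r)/2)(7/6)] × 2.365/2.306. At r = 0.4 this is √(0.70 × 1.1667) × 1.0256 = 0.904 × 1.0256 = 0.93.

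A simulation of 40,000 trials per value of r, in the same layout, gave the mean widths behind the third and fourth columns. In units of the ward-mean SD, the change and adjusted widths were, for example, 2.825 and 2.591 at r = 0.4.

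| r | Adjusted/change, formula | Adjusted/change, simulated | Adjusted/follow-up only, simulated | Change/follow-up only, √[2(1 − r)] | Fraction of imbalance carried, 1 − r |
|---|---|---|---|---|---|
| 0.2 | 0.86 | 0.85 | 1.07 | 1.26 | 0.8 |
| 0.4 | 0.93 | 0.92 | 1.00 | 1.10 | 0.6 |
| 0.5 | 0.96 | 0.95 | 0.95 | 1.00 | 0.5 |
| 0.6 | 0.99 | 0.98 | 0.87 | 0.89 | 0.4 |
| 0.7 | 1.02 | 1.01 | 0.78 | 0.77 | 0.3 |
| 0.9 | 1.08 | 1.07 | 0.48 | 0.45 | 0.1 |

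The formula compares root-mean-square widths, which is why it sits about 0.01 above the ratio of mean widths. Its limit as r approaches 1 is √(7/6) × 1.0256 = 1.11.

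**Step 4: break-even.** Variances are equal at (1 + r)/2 × 7/6 = 1, so r = 12/7 − 1 = 0.71. Formula widths are equal near r = 0.63. The simulated widths cross between 0.6 and 0.7.

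**Step 5: chance imbalance.** The SD of the baseline difference between arms is √(1/3) = 0.58 ward-mean SDs. At r = 0.4, an imbalance of that size moves the expected change-score difference by 0.6 × 0.58 = 0.35 SD in the opposite direction. In the simulation the slope of the change estimate on the imbalance was −(1 − r); for the adjusted estimate it was about 0.

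**The case against.** The strongest reply is that little hangs on this. The section itself calls the analysis descriptive, no decision rule uses QUIS, and PEECH is primary. That stands, and it limits the weight of the point. It does not make the noisier estimate preferable, since the protocol still presents differences through confidence intervals.

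Second, the size rests on assumed correlations, and the advantage reverses when ward levels are very stable. That also stands. In addition, the eight sessions are spread over mornings, mealtimes and visiting periods, and follow-up repeats the same methods. If the mix of session types is alike in both periods, variation between types is not noise in the change, and r would be higher than Step 1 gives for the same raw ICC. The protocol does not settle this.

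Third, the condensed text does not name even the intervention term, so its list of covariates may be incomplete. If baseline were already in the change model, the arm estimate would equal the one recommended here. That is possible, but nothing in the article shows it.

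Three stronger readings are tempting and not supported:
- **That the change score is biased.** It is unbiased over repeated randomisations; the imbalance effect is conditional on the observed baselines and is not a second defect.
- **That QUIS departs from a baseline-adjusted norm in this protocol.** The main model for the healthcare assistant outcomes has the intervention as its only fixed effect, and "the baseline value of the outcome will also be included as a fixed effect in a sensitivity analysis". Patient-level adjustment is only where appropriate.
- **That the variance of change will mislead the planning of the definitive trial.** No section says that it will be used for that, and data from both periods allow other variances and r to be computed.

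**Conclusion.** The point holds as a modest, cheap improvement. For r from 0.2 to 0.5, which corresponds roughly to session ICCs of 0.05 to 0.20 with ward stability of 0.8, baseline adjustment narrows the interval by about 14% to 4%. Near r = 0.65 the two methods are equal. Above that the change score is slightly better: adjustment is about 2% wider at r = 0.7 and 8% wider at r = 0.9. The word *usually* therefore has to stay.

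Both intervals are wide whatever is done: at r = 0.5 the full widths are 2.58 and 2.45 ward-mean SDs. When r is below about 0.4, ignoring baseline would be narrower still, although that estimate too would move with chance imbalance, by r per unit.

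The conclusion assumes ward-level analysis, equal variances in the two periods, and an r that the protocol does not give.

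**What to change.** In Ward-level analysis, replace the change-score model with this: the ward's mean QUIS at follow-up is the outcome, with the ward's mean baseline QUIS, arm and Trust as terms. Keeping change as the outcome and adding the baseline mean as a covariate gives the same arm estimate and would do equally well. Report the ward-level correlation between baseline and follow-up as a planning parameter, and show change in a descriptive column.

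No data collection or design feature changes. The cost is one of eight residual degrees of freedom, and an interval a few percent wider, about 8% at r = 0.9, if r turns out to exceed about 0.65.
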